## **1 LIST OF ABBREVIATIONS**

|        |                                                                           |
|--------|---------------------------------------------------------------------------|
| ACR    | American college of rheumatology                                          |
| AE     | Adverse event                                                             |
| BDMARD | Biological disease modifying anti-rheumatic drug                          |
| CCP    | Cyclic citrullinated peptide antibody                                     |
| CRF    | Case report form                                                          |
| CRP    | C-reactive protein                                                        |
| DAS28  | Disease activity score with 28 joint count                                |
| DMARD  | Disease modifying anti-rheumatic drug                                     |
| EC     | Ethics committee                                                          |
| ESR    | Erythrocyte sedimentation rate                                            |
| EULAR  | European league against rheumatism                                        |
| FSH    | Follicle-stimulating hormone                                              |
| GCP    | Good Clinical Practice                                                    |
| GnRH   | Gonadotropin-releasing hormone                                            |
| HAQ    | Health assessment questionnaire                                           |
| HCG    | Human chorionic gonadotropin                                              |
| HIV    | Human immunodeficiency virus                                              |
| HPG    | Hypothalamic-pituitary-gonadal                                            |
| ICH    | International Conference on Harmonisation                                 |
| IL     | Interleukin                                                               |
| IP     | Interphalangeal                                                           |
| IVRS   | Interactive voice response system                                         |
| LH     | Luteinising hormone                                                       |
| LHRH   | Luteinising hormone-releasing hormone                                     |
| MA     | Medicines agency                                                          |
| MIP    | Macrophage inflammatory protein                                           |
| MCP    | Metacarpophalangeal                                                       |
| MCP    | Monocyte chemoattractant protein                                          |
| mRNA   | Messenger ribonucleic acid                                                |
| MTX    | Methotrexate                                                              |
| NSAID  | Non-steroidal anti-inflammatory drug                                      |
| PIP    | Proximal interphalangeal                                                  |
| RA     | Rheumatoid arthritis                                                      |
| REK    | Regional ethics committee (Regional komité for medisinsk forskningsetikk) |
| SAE    | Serious Adverse Events                                                    |
| s.c.   | Subcutaneous                                                              |
| SD     | Standard deviation                                                        |
| SJC    | Swollen joint count                                                       |
| SLE    | Systemic lupus erythematosus                                              |
| SLV    | Norwegian medicines agency (Statens legemiddelverk)                       |
| SUSAR  | Suspected unexpected serious adverse reaction                             |
| TJC    | Tender joint count                                                        |
| TNF    | Tumour necrosis factor                                                    |
| VAS    | Visual analogue scale                                                     |

## **2 BACKGROUND**

### **2.1 Rationale of study**

Rheumatoid arthritis (RA) affects up to 1 % of the world's population and is associated with significant morbidity and mortality. It is a chronic inflammatory disease characterized by infiltrating leukocytes in the synovium, progressive cartilage destruction and bone erosion. Despite major advances in the treatment for RA, patients do not always qualify for, do not always tolerate, or experience an insufficient response to currently available therapy. This study investigates a novel method of treating RA and can aid in the understanding of hormones in RA.

### **2.2 Hypothesis**

The aetiology of RA is thought to be genetically, environmentally and hormonally related. Hormonal mechanisms, contributing to RA pathophysiology are not fully understood. However, bidirectional mechanisms between the endocrine and immune systems have been described previously.

RA tends to develop, flare or subside during changes in hypothalamic pituitary gonadal (HPG) axis function such as the menstrual cycle, pregnancy, postpartum, and the menopause. All of these situations are associated with substantial changes in the secretion of hormones of the HPG axis which are regulated primarily by the hypothalamic hormone, gonadotropin-releasing hormone (GnRH). GnRH has been shown to be immunostimulatory, (see section 2.3) and perhaps GnRH contributes to changes in disease activity observed during such hormonal changes. Therefore it is possible that treatment with GnRH-antagonists may reduce RA activity.

[figure not shown]

### 2.3 Summary of findings from studies that are relevant to the trial

GnRH receptor and GnRH mRNA expression has been identified in human peripheral lymphocytes suggesting a potential autocrine and/or paracrine effect of GnRH in immune system regulation. Human peripheral T cells (CD4+, CD8+) and the leukaemic (Jurkat) cell line similar to T lymphocytes have been shown to produce immunoactive and bioactive GnRH. GnRH *agonists* have been reported to increase thymus weight in adult rats. In contrast, GnRH *antagonists*, blocked thymocyte proliferative responses and decreased CD4+ percentages and thymus weights in neonatal rats.

GnRH *antagonists* might also act on the immune system through B- lymphocytes, for example GnRH antagonists decreased B cell percentages and ameliorated murine lupus independently of gonadal sex hormone secretion in castrated mice, whereas GnRH *agonists* increased lupus disease severity in gonadectomised mice of both sexes. GnRH may also act indirectly through changes in pituitary hormones (luteinising hormone [LH] and follicle-stimulating hormone [FSH]). Indeed in vitro studies have shown that both LH and FSH have a stimulatory effect on IL-2 induced stages of T-cell activation. Furthermore, FSH directly stimulated tumour necrosis factor (TNF)- $\alpha$  production from bone marrow granulocytes and macrophages. Notably, significant associations have been observed between percent

changes from baseline, of gonadotropins (LH and FSH) and RA disease activity, and between gonadotropins and key cytokines (i.e. TNF-  $\alpha$ ) in RA patients.

## **2.4 Name and Description of Investigational Product**

There are several GnRH-antagonists available. The two most common GnRH-antagonists in clinical studies are cetrorelix and ganirelix. Cetrorelix was preferred as there is more clinical data available on cetrorelix, and cetrorelix has a higher suppressive rate per milligram of peptide than other antagonists.

*GnRH-Antagonist:*

‘Cetrorelix’

*Approved Name:*

‘Cetrorelix Acetate’

*Brand Name:*

‘Cetrotide’ ASTA Medica

*Therapeutic Class:*

‘Gonadotropin-releasing hormone antagonist’ Cetrorelix is a GnRH antagonist which competitively blocks the binding of GnRH to GnRH receptors. This results in a dose-dependent suppression of the release of gonadotropins i.e. LH and FSH.

*Licensed Indications:*

Prevention of premature ovulation in patients undergoing controlled ovarian stimulation followed by oocyte pick-up and assisted reproductive techniques.

*Pharmacology:*

Cetrorelix is a decapeptide and a potent GnRH antagonist. It competitively inhibits the secretion of LH and FSH from the pituitary gland. Female and male volunteer studies show that cetrorelix produces a dose-dependent suppression of FSH, LH and oestradiol that is

maintained throughout continuous treatment and is reversible after treatment discontinuation. Cetrorelix and GnRH antagonists in general, have an advantage over GnRH agonists in that they lack the initial flare up of gonadotropins and therefore have a shorter treatment period.

## **2.5 Previous Studies Investigating Safety**

### **2.5.1 Previous Studies Investigating Safety in Males**

Cetrorelix has been tested in males, as well as females. Behre et al administered 1.0, 2.0, and 5.0 mg of subcutaneous cetrorelix in 30 healthy males. LH and testosterone were suppressed; maximal suppression occurring 4-6 h after injection. Hormone levels returned to normal within 24 hours after the 1.0 and 2.0mg doses; and within 48 hours for the 5.0mg dose. The only side effect observed after the administration of cetrorelix was a transient local erythema at the injection site that disappeared with 30 minutes. No changes in vital signs, clinical chemistry, whole blood count, or urinalysis were found. GnRH-antagonists have been studied as potential treatments for prostate cancer, benign prostatic hypertrophy and male contraception.

### **2.5.2 Previous Studies Investigating Safety in Pre-menopausal and Postmenopausal Females**

Pre-menopausal and postmenopausal female volunteer studies show that cetrorelix produces a dose-dependent suppression of FSH, LH and oestradiol that is maintained throughout continuous treatment and is reversible after treatment discontinuation. A single injection during the late follicular phase delays the LH surge, even in cases where the surge has already begun. This data also showed that cetrorelix was well tolerated. Another study examined the effects of daily GnRH antagonist during the periovulatory period. Injections of

10mg/day on 2, 3 and 5 consecutive days were administered. In half of the patients, demise of the dominant follicle was observed and a new cycle was initiated. In the other half of the patients, ovulation was delayed but not inhibited. Cetrorelix has also been administered to women in the late luteal phase which reduces the pace of follicular development. In general, whatever phase of the menstrual cycle, GnRH antagonists give an immediate receptor blockage of gonadotrophic cells, which causes an immediate , but reversible, subsequent decrease of LH, FSH and oestradiol secretion for approximately 1-4 days after a single dose. The weekly administration (i.e. in all phases of the menstrual cycle) of 3mg of cetrorelix in women with endometriosis was effective and safe.

## **2.6 Known Risks**

Common (>1/100) side effects are from the injection site, for example, irritation, itch or redness. Less common side effects are nausea and headache. Rare (<1/1000) side effects are intense itching on the skin and serious hypersensitivity reactions, including anaphylactic reactions.

## **3 AIM**

### **3.1 Primary Aim**

The primary aim of this study is to assess whether cetrorelix acetate therapy can give a beneficial clinical response (measured by the change from baseline in the disease activity score calculated with C-reactive protein levels [DAS28CRP]) in RA patients with moderate to severe disease activity, and therefore be of future therapeutic benefit. For comparison, it was considered necessary to include a placebo group.

### **3.2 Secondary Aims**

Secondary aims of this study include:

- To assess whether cetrorelix is safe in rheumatoid arthritis patients.
- To assess whether cetrorelix acetate can decrease acute phase reactants (C-reactive protein [CRP], erythrocyte sedimentation rate [ESR]), anti-cyclic citrullinated peptide (anti-CCP) antibody levels and cytokine levels in RA patients.
- To assess whether cetrorelix can give a beneficial clinical response using American College of Rheumatology (ACR) response criteria ‘ACR20/50/70/(90)’, and European League Against Rheumatism (EULAR) response criteria ‘Good’, ‘Moderate’, ‘None’, and the proportion of DAS28CRP low disease activity/remission.
- To assess whether cetrorelix can decrease disability (measured by the Health Assessment Questionnaire [HAQ] score).
- To gain an increased understanding of the role of GnRH in the pathogenesis of RA.

## **4 STUDY DESIGN**

### **4.1 Overview of Study Design and Rationale for Study Design**

This study is a proof-of-concept, double-blind, randomised, placebo-controlled design to assess the efficacy and safety of cetrorelix acetate in the treatment of RA patients.

A total of 98 patients with a diagnosis of RA fulfilling study eligibility criteria will be enrolled at Betanien Hospital, Skien, Norway. Study medications cetrorelix acetate

(5mg/d for the first two days and 3mg/d for the following 3 days, in total 5 consecutive days of medication) or placebo sodium chloride solution 5ml/d for the first 2 days and 3ml/d for the following 3 days will be administered subcutaneously by the research nurse. Efficacy and safety measurements will be performed throughout the study from baseline to day 15. There is a screening period of 28 days.

As hypothalamic suppression of reproductive function has not been investigated in RA before, the intervention is limited to a short period. Previous studies suggest that after a threshold of approximately 3–5mg s.c., increasing the dose does not significantly increase the antagonistic effect of cetrorelix on GnRH receptors. However, repeated doses with short time intervals both increase *and* prolong the antagonistic effect of cetrorelix.

#### **4.2 Number of Patients/Assignments to Treatment Groups**

98 patients will be recruited into this study and will be randomised equally into the 2 intervention groups. Patients will be stratified by sex to avoid any random gender bias between the two groups. There will be no replacement of patients should a patient's treatment be discontinued for any reason.

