#### **4.3 Patient Randomisation and Enrolment**

Patients will be evaluated for eligibility to ensure the criteria in section 5.2 and 5.3 are filled. All patients must sign the Informed Consent form prior to screening. A screening form will be filled for each patient. Eligible patients will be randomised, through computer generated allocation, prior to receiving any study medication; this is carried out by study personnel who are not involved with outcome assessments. Randomisation

will be carried out in dynamic blocks (varying block sizes unknown to the study site), and stratified for sex. Once a patient has been through the screening process and has given informed consent for participation, the research nurse obtains randomisation information by calling an offsite central office. The patient will be provided with a unique medication number and randomisation number. As confirmation, the investigator will be provided with a posted verification of each patient's registration.

A patient's treatment assignment should only be unblinded when knowledge of the treatment is essential for the further management of the patient.

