## 5.2 Inclusion Criteria

A subject will be eligible for study participation if he/she meets the following criteria:

- Age  $\geq 18$  years
- Fulfilment of the revised 1987 American College of Rheumatology (ACR) criteria for the classification of RA.
- Moderate or severely active RA, defined as a DAS28  $\geq 3.2$  and at least two of the following criteria:  $\geq 6$  painful joints,  $\geq 3$  swollen joints, ESR  $\geq 20$ mm/h, and a C-reactive protein  $\geq 10$ mg/L
- Prednisolone  $\leq 7.5$ mg/day permitted if stable for at least 4 weeks prior to baseline, NSAIDs permitted if stable for at least 2 weeks prior to baseline; disease modifying anti-rheumatic drugs (DMARDs) permitted if stable for at least 8 weeks prior to baseline
- A negative pregnancy test for women of childbearing potential prior to start of treatment
- Use of reliable method of contraception e.g. intra-uterine devices or sheaths by all sexually active patients. If the patient is abstinent, they must agree to stay abstinent or use reliable contraception if sexual activity commences.
- Menstruating women may enter the study in the early follicular phase of their menstrual cycle only
- Able and willing to give written informed consent and to comply with the requirements of the study protocol

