## **9 STATISTICS**

### **9.1 Sample Size**

Assuming a difference of 0.6 unit reduction from baseline in mean DAS28 score on cetorelix compared with placebo and an underlying standard deviation for the changes from baseline of 1.0 unit (from previous data), we calculated that

$$N = 2(Z_{\alpha} + Z_{\beta})^2 \sigma^2 / \delta^2,$$

where  $\delta = \mu_2 - \mu_1 = 0.6$

$$N = 2 (1.96 + 0.842)^2 1^2 / 0.6^2$$

**N= 44** per treatment group

To allow for drop-outs, **49 patients in each group** were considered adequate. The significance is 0.05 (two-tailed) with a power of 0.8.

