### **9.3.2 Primary Endpoint and Analysis**

Cetrorelix has a rapid onset and offset effect; therefore we have chosen an early primary endpoint. The primary endpoint is the change in disease activity score (DAS28CRP) on Day 5b (12 hours after the last injection [time point when LH and FSH levels are expected to be lowest]).

The primary variable will be analysed by ANCOVA, linear regression with last measurement (in this case day 5b) as the dependent variable and treatment and baseline measurement as independent variables (covariates).

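### The primary ANCOVA leaves out sex, the factor the trial stratifies on, and menopausal status, which is known before dosing and plausibly prognostic

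*Protocol*

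**What the plan says.** **Randomisation.** Protocol 4.2: "98 patients will be recruited into this study and will be randomised equally into the 2 intervention groups", and "Patients will be stratified by sex to avoid any random gender bias between the two groups". Protocol 4.3 repeats that randomisation "will be carried out in dynamic blocks (varying block sizes unknown to the study site), and stratified for sex". No other stratification factor is named.

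**Primary analysis.** Protocol 9.3.2 regresses day 5b DAS28CRP on "treatment and baseline measurement as independent variables (covariates"). Sex is not in the model, and neither is menopausal status. Items 1, 2, 3, 9 and 10 of 9.3.3 (DAS28, biomarkers, ACR core set, HAQ, anti-CCP) take their ANCOVA from 9.3.2.

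**Who is enrolled.** Men, premenopausal women and postmenopausal women are all eligible. Section 5.2 restricts timing for one group: "Menstruating women may enter the study in the early follicular phase of their menstrual cycle only". Section 6.3 requires a urine pregnancy test for premenopausal women before dosing. The site therefore has to know each woman's status before treatment starts.

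**Rationale.** Section 2.2: "RA tends to develop, flare or subside during changes in hypothalamic pituitary gonadal (HPG) axis function such as the menstrual cycle"; the same sentence goes on to name the menopause. Section 2.3 cites associations in RA patients between percent "changes from baseline, of gonadotropins (LH and FSH) and RA disease activity".

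**The concern.** Section 4.2 decides that one factor deserves protection from chance imbalance, and 9.3.2 then leaves that factor out of the model. Balance bought by stratification but not carried into the analysis is partly wasted: if the factor is prognostic, its variance stays in the residual and the standard error is larger than it needs to be.

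A second baseline variable is known at no extra cost. The rationale ties RA activity to changes in the HPG axis, and the entry rule for menstruating women shows that cycle state was thought to matter. Pre- and postmenopausal women nevertheless share one stratum, so their mix can differ between arms by chance, and the stated model does not correct for it.

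At stake is a little precision, and how easily the result can be defended if a visible imbalance occurs. The validity of the randomised comparison is not at stake.

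**Working it through.** **1. The plan's own figure.** Protocol 9.1 uses a difference of 0.6, an SD of change of 1.0, two-sided 0.05 and power 0.80.

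N = 2(1.96 + 0.842)² × 1² / 0.6² = 43.6, so 44 per arm. This reproduces. Power = Φ(0.6/√(2/44) − 1.96) = 80.4% at 44 per arm, and 84.4% at 49.

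**2. Chance imbalance within the female stratum.** The protocol gives no share of women and no menopausal mix. Assumed: 68-80 of the 98 are women, and 50-80% of these are postmenopausal. With W women split equally and a fraction p postmenopausal, the number in one arm is hypergeometric. The between-arm difference in count has

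SD = W × √(p(1−p)/(W−1)).

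| Women W | Postmenopausal | SD of difference | P(difference ≥ 5) | 1.96 × SD / 49 |
|---|---|---|---|---|
| 68 | 54 (about 80%) | 3.36 | 0.13 | 0.134 |
| 74 | 48 (about 65%) | 4.13 | 0.22 | 0.165 |
| 74 | 37 (50%) | 4.33 | 0.35 | 0.173 |
| 80 | 40 (50%) | 4.50 | 0.26 | 0.180 |

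Over the whole grid the SD is 3.4-4.5 patients, the chance of a difference of 5 or more is 13-35%, and the 95% limit is 13-18 percentage points of an arm of 49.

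**3. What that does to the contrast.** Shift = imbalance × prognostic gap. The gap in expected DAS28 change between pre- and postmenopausal women is an assumption, taken as 0.3-0.5. For the middle mix (74 women, about 65% postmenopausal):

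- 0.165 × 0.3 = 0.05
- 0.165 × 0.5 = 0.08

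This is 8-14% of the 0.6 in "Assuming a difference of 0.6 unit reduction from baseline in mean DAS28 score on cetorelix compared with placebo". At the extremes of the grid the shift is 0.134 × 0.3 = 0.04 and 0.180 × 0.5 = 0.09. The standard error of the contrast is √(2/49) = 0.20, so 0.05-0.08 is 0.25-0.4 of a standard error, and only at the 95% limit of imbalance.

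**4. Precision.** Treat the SD of 1.0 as including the gap. The variance explained by menopausal status among women is v = g² × m(1−m) × f, where g is the gap, m the premenopausal share of women and f the share of women in the trial. Power is then Φ(0.6/√((1−v) × 2/44) − 1.96). The ranges below cover (f, m) = (0.7, 0.3), (0.8, 0.3) and (0.7, 0.5).

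| Gap g | v | Power at 44 per arm |
|---|---|---|
| 0 | 0 | 80.4% |
| 0.2 | 0.006-0.007 | 80.6% |
| 0.3 | 0.013-0.016 | 80.9-81.0% |
| 0.5 | 0.037-0.044 | 81.8-82.1% |
| 0.8 | 0.094-0.112 | 84.1-84.8% |

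Any gain from sex itself would be additional. The protocol gives no figure from which to size it.

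**5. Validity.** The planned ANCOVA was simulated with 98 patients, 70 of them women and about 35% of these premenopausal, using 3,000 runs per scenario. Stratification was by sex only, with no menopausal adjustment. Type I error was 5.3%, 4.4% and 4.7% for gaps of 0, 0.5 and 0.8, where the simulation error is about 0.4 points. With a true effect of −0.6 the mean estimates were −0.600, −0.600 and −0.595. The estimate is unbiased and the test holds its level. When the simulation stratified on all three levels but left the factor out of the model, type I error fell to 3.0% at a gap of 0.8. Stratifying on a prognostic factor without adjusting for it makes the test conservative.

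**The case against.** **Chance imbalance is ordinary random error.** The standard error already carries it. This stands, and the simulation confirms it: no bias, level kept, sample size unaffected.

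**The size is assumed and small.** The mix and the gap are both assumptions, and with no gap the menopausal split gains nothing. This stands too, and is why the point concerns a cheap improvement and not an error.

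**Hormonal variation is already limited.** Menstruating women enter in one cycle phase only (5.2), hormone replacement and oral contraception are excluded (5.3), and the primary endpoint falls less than five days after baseline. This reduces the likely gap. It does not make cycling women comparable with postmenopausal women.

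**The menopausal classification is undefined.** Sections 5.2 and 6.3 and Figure 1 use several terms for overlapping groups of women. This also stands, so a definition is part of the fix.

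**A statistical analysis plan might add covariates.** It might. But 9.3.2 states the primary model outright, and that model omits the protocol's own stratification factor.

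**Stronger readings the protocol does not support:**

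- A reader might infer that menopausal status is said to determine RA activity or how much the drug can do. Section 2.2 is tentative and speaks of changes in HPG function. No section says the drug effect differs by menopausal status.
- A reader might take 2.5.2 as setting the two groups of women apart. It reports the same hormone suppression for both.
- A reader might expect between-arm hormone comparisons to be distorted. Section 9.3.3 lists none; hormones enter only through the rank correlations of item 8.

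**Conclusion.** The primary ANCOVA should contain the factor used to stratify, and can take menopausal status with it at almost no cost. As written it does neither. The effect is modest: a shift of about 0.05-0.08 DAS28 units at the 95% limit of imbalance for an assumed gap of 0.3-0.5, and power of 81-82% instead of 80.4% at 44 per arm for gaps of 0.2-0.5. These figures rest on assumed shares of women and of postmenopausal women and on an assumed gap, none of which the protocol supplies. There is no systematic bias, no inflation of type I error, and no reason to change the 44 or 49 per arm. Stratifying by sex alone is a defensible choice. The weakness lies in the model, and the improvement is worth making because it is nearly free.

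**What to change.** 1. In 9.3.2, add a three-level baseline factor to the ANCOVA: men, premenopausal women, postmenopausal women. It contains sex, so the stratification factor is then in the model.
2. Carry the same factor into the ANCOVAs of 9.3.3 that refer to 9.3.2 (items 1, 2, 3, 9 and 10).
3. Write one definition of menopausal status that places every woman in exactly one level, record it before randomisation, and reconcile the differing terms in 5.2, 6.3 and Figure 1 with it.
4. Optional, if the randomisation list is not yet fixed: stratify by the same three-level factor in 4.2 and 4.3. If this is done, step 1 becomes necessary, because the test is conservative without it.

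**Cost.** Two degrees of freedom: with 98 patients the residual goes from 98 − 3 = 95 to 98 − 5 = 93. No new visit, sample or patient is needed. The real work is the definition. Step 4 adds one question to the call to the central randomisation office, and one more stratum that may end in an incomplete block.
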